## Abstract

**Background:**

Healthy lifestyles may help to delay arterial aging. The purpose of this study is to analyze the relationship of physical activity and dietary pattern to the circadian pattern of blood pressure, central and peripheral blood pressure, pulse wave velocity, carotid intima-media thickness and biological markers of endothelial dysfunction in active and sedentary individuals without arteriosclerotic disease.

**Methods/Design:**

**Design: **A cross-sectional multicenter study with six research groups.

**Subjects: **From subjects of the PEPAF project cohort, in which 1,163 who were sedentary became active, 1,942 were sedentary and 2,346 were active. By stratified random sampling, 1,500 subjects will be included, 250 in each group.

**Primary measurements: **We will evaluate height, weight, abdominal circumference, clinical and ambulatory blood pressure with the Radial Pulse Wave Acquisition Device (BPro), central blood pressure and augmentation index with Pulse Wave Application Software (A-Pulse) and SphymgoCor System Px (Pulse Wave Analysis), pulse wave velocity (PWV) with SphymgoCor System Px (Pulse Wave Velocity), nutritional pattern with a food intake frequency questionnaire, physical activity with the 7-day PAR questionnaire and accelerometer (Actigraph GT3X), physical fitness with the cycle ergometer (PWC-170), carotid intima-media thickness by ultrasound (Micromax), and endothelial dysfunction biological markers (endoglin and osteoprotegerin).

**Discussion:**

Determining that sustained physical activity and the change from sedentary to active as well as a healthy diet improve circadian pattern, arterial elasticity and carotid intima-media thickness may help to propose lifestyle intervention programs. These interventions could improve the cardiovascular risk profile in some parameters not routinely assessed with traditional risk scales. From the results of this study, interventional approaches could be obtained to delay vascular aging that combine physical exercise and diet.

**Trial Registration:**

Clinical Trials.gov Identifier: NCT01083082

## Background

Aging is associated with an increase in arterial stiffness that can be assessed using different tools, such as the increase in pulse pressure, both clinical and ambulatory, changes in circadian pattern of blood pressure, increased pulse wave velocity and central blood pressure, as well as certain biological markers of endothelial dysfunction[1-3].

Blood pressure measurement at the clinic is still currently the standard of reference, but there is increasing evidence that the values obtained after home blood pressure measurement by the patient and particularly 24-hour ambulatory blood pressure monitoring (ABPM) show a better correlation with target organ damage[4] and with cardiovascular events[5,6]. It has been observed that the prognostic value of blood pressure during rest is greater than during activity [7,8] and that a greater variability blood pressure is associated with increased target organ damage[9].

The accepted gold standard to assess arterial stiffness is currently femoral carotid pulse wave velocity (PWV) [1] and it has been related to increased morbidity and mortality in both patients with cardiovascular disease and in healthy subjects[10,11]. It has also been noted that central blood pressure is more strongly related than peripheral blood pressure to cardiovascular morbidity and mortality[12]. The index of increase of central blood pressure, or augmentation index (AIx), is an indicator of central arterial stiffness, which, together with aortic systolic blood pressure and aortic pulse pressure, complements the information obtained with pulse wave velocity to assess arterial stiffness. This index is closely related to both physiological arterial aging and premature aging from certain diseases, though in some studies there are discrepancies in the results obtained[13]. In the ASCOT study [14], increased morbidity and mortality was found in one of the study groups compared to the other, despite the fact that peripheral blood pressures were similar in both groups. In the CAFE sub-study [15], it was found that subjects with greater central blood pressure and AIx had greater morbidity and mortality.

Serum levels of osteoprotegerin (OPG) are elevated in patients with type 1 and 2 diabetes [16,17] from early stages and contribute to the endothelial dysfunction associated with the disease. The OPG has also been found to be associated as a subclinical marker of atherosclerosis in women with postmenopausal osteoporosis and in general population[2,18]. In addition, endoglin levels are decreased in diabetics and are also related to the severity of the vascular involvement[19].

The potential benefits enjoyed by active people, both at the biological and psychological level, range from a better quality of life to a reduction in the risks associated with hypertension, diabetes, cardiovascular diseases and all causes of mortality[20-22]. Some studies have shown a decrease in ambulatory blood pressure with physical exercise[23,24], but the relationship to circadian pattern has not been adequately studied. Aerobic exercise may attenuate arterial hardening as was seen in the Baltimore Longitudinal Study, where elderly male athletes had a PWV, AIx and systolic blood pressure lower than sedentary subjects[25], and it has been associated with a reduced atherosclerosis progression in humans[26]. Improvement of carotid artery elasticity has also been noted in previously sedentary subjects who started a physical exercise program[3]. However, such a clear relationship of arterial stiffness to exercise has not been found in post-menopausal women[27], or in adults with chronic high blood pressure[28]. In addition, it has been observed that high-intensity endurance exercise may be associated with an increase in arterial stiffness[29,30], although this effect could be countered with the performance of aerobic exercise[31].

Therefore, there are still some unresolved issues, such as the effect on vascular structure and function of endurance exercise, alone or combined with aerobic exercise, recommended for maintenance of muscular strength in the elderly[32]. The effect of different doses of exercise on arterial stiffness, circadian pattern of blood pressure, or central blood pressure has not been adequately studied. Finally, in elderly patients with cardiovascular disease, aerobic exercise improved endothelial function[33]. This effect has not been studied or the results are not consistent in healthy subjects[32,34].

There is evidence that the Mediterranean diet (Mediterranean/DASH diet) with high consumption of fruit and vegetables, fish and olive oil may have a positive effect on endothelial function[35-37], as well as on the reduction of peripheral blood pressure[38,39]. However, the effect of dietary patterns on the circadian pattern of blood pressure, particularly on the nocturnal decrease and variability, has not been established, and the influence of these patterns on the biological markers to be analyzed such as OPG and endoglin has also not been clarified. An association has been found between the Mediterranean diet and vascular structure analyzed by carotid intima-media thickness[40]. However, although a decrease in central blood pressure has been found in obese patients subjected to a low-calorie diet[41], the relationship of different dietary patterns with PWV or AIx has not been studied in healthy subjects.

Therefore, the purpose of this study is to analyze the relationship of different doses of physical activity, fitness and dietary pattern to the circadian pattern of blood pressure, vascular structure and function analyzed by PWV and AIx, carotid intima-media thickness and biological markers of endothelial dysfunction (OPG and endoglin). This study continues the research line of the project "Multicenter Assessment of Experimental Program Promoting Physical Activity (PEPAF)" [42,43], focusing on the cardiovascular benefits obtained with healthy lifestyles, taking advantage of the patient cohort of this study and the infrastructure and expertise of the research teams.

### Objectives

1. To analyze the relationship of physical activity and fitness to circadian pattern of blood pressure, central and peripheral blood pressure, PWV, AIx, and carotid intima-media thickness in active and sedentary individuals without arteriosclerotic disease.

2. To analyze the relationship of caloric intake and food pattern to circadian pattern of blood pressure, central and peripheral blood pressure, PWV, AIx and carotid intima-media thickness in active and sedentary individuals without arteriosclerotic disease.

3. To study the correlation of OPG and endoglin levels with arterial stiffness assessed by PWV and AIx, as well as with circadian pattern of blood pressure and carotid intima-media thickness in subjects with different level of physical activity and different nutritional patterns.

## Methods/Design

### Design

A cross-sectional study, to evaluate the association of lifestyles (diet and exercise) with circadian pattern of blood pressure, arterial stiffness and endothelial function in a previously established cohort of healthy subjects with different levels of physical activity. This is a multi-center study with the participation of six groups distributed throughout Spain with the purpose of increasing the sample size to test the proposed hypotheses and to increase the external validity of the study.

### Subjects

#### Study population

Subjects will be selected from the PEPAF project cohort[39,40]. This is a cohort composed of 5,451 subjects identified at the start of the study and divided into three physical activity exposure levels: A) 1,163 sedentary in 2003, who became active in 2006, B) 1,942 who remained sedentary during the 24 months of follow-up, and C) 2,346 who were active at baseline assessment. The study will include subjects aged 20-80 years who agree to participate in this study and sign the informed consent. The exclusion criteria were: known coronary or cerebrovascular atherosclerotic disease, heart failure, moderate or severe COPD, walking-limiting musculoskeletal disease, advanced respiratory, renal or hepatic disease, severe mental diseases, treated oncological disease diagnosed in the past 5 years, pregnant women and terminal patients.

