#### Evaluation of peripheral artery involvement

This will be evaluated using the ankle-brachial index (ABI), performed in the morning without having consumed coffee or tobacco for at least 8 hours prior to measuring and an ambient temperature of 22-24°C. With the feet uncovered, in a supine decubitus position after 20 minutes of rest, the pressure in the lower extremities was measured using a portable Doppler system Minidop Es-100Vx (*Hadeco, Inc. Arima, Miyamae-ku, Kawasaki, Japan*) applying the probe at the anterior or posterior tibial artery at an angle of approximately 60° to the direction of blood flow. The transducer's cuff will be quickly inflated in each ankle about 30 mmHg above the systolic pressure and the pressure will be allowed to descend (by about 2 mmHg per second) until the first sound corresponding to the systolic pressure was heard. The blood pressure will be also measured in both arms (measured twice at 3-5 minute intervals). The ABI will be calculated separately for each foot by dividing the higher of the two systolic pressures in the ankle by the highest measurement of the two systolic pressures in the arm [48].

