### Methodological limitations

The main limitation in the first phase of the study is that it is a cross-sectional design and therefore only allows detection of association and not causal relationship. This problem is expected to be solved in the second phase with randomized clinical trial that is planned. Selection of the sample was randomized and so it would ideally represent the population without cardiovascular disease seen in primary care, but the losses suffered by the cohort during follow-up were close to 20% and this may have influenced the representativeness of the population attending primary care centers.

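### Objectives 1 and 2 are about people free of arteriosclerotic disease, but the exclusion list leaves people with known peripheral arterial disease eligible

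*Protocol article*

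**What the plan says.** Three sections of the protocol article describe the intended population:

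- Objectives 1 and 2 refer to "carotid intima-media thickness in active and sedentary individuals without arteriosclerotic disease". Objective 3 carries no such restriction.
- The Design section places the study "in a previously established cohort of healthy subjects with different levels of physical activity".
- Methodological limitations says of the randomly selected sample that "it would ideally represent the population without cardiovascular disease seen in primary care".

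Eligibility is set under Study population. It opens with "The study will include subjects aged 20-80 years who agree to participate in this study" and continues: "The exclusion criteria were: known coronary or cerebrovascular atherosclerotic disease, heart failure, moderate or severe COPD". The list then runs on through "walking-limiting musculoskeletal disease, advanced respiratory, renal or hepatic disease, severe mental diseases" and ends with recently treated cancer, pregnancy and terminal illness.

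The leg arteries appear elsewhere. A section headed for peripheral artery involvement states "This will be evaluated using the ankle-brachial index (ABI" and gives the measurement technique. Other variables records each participant's personal history of cardiovascular diseases. The article does not tie either item to eligibility.

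**The concern.** The exclusions cover known atherosclerotic disease in two vascular beds, while the population in objectives 1 and 2 is defined without reference to any bed. Someone with diagnosed leg artery disease meets the entry rules yet lies outside the population about which the study wants to draw conclusions.

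The omitted condition is not neutral here. The exposure is time spent in moderate or vigorous activity, and anyone below the threshold is classed as sedentary. The outcomes are AIx, pulse wave velocity and carotid intima-media thickness. Leg artery disease may reduce walking and may go with stiffer, thicker arteries. That is general clinical knowledge, which the article does not state, and I treat it as an assumption. If it holds, part of any sedentary-active difference could reflect disease that lowered activity, not activity related to arterial condition. The list already removes people whose walking is limited by a musculoskeletal problem, so leaving in a vascular cause, which is also linked to the outcomes, is hard to justify.

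**Working it through.** **Comparison of the text**

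| Point | Stated population | Exclusion list |
|---|---|---|
| Arterial disease | None (objectives 1 and 2); healthy (Design); no cardiovascular disease (Methodological limitations) | Known disease, coronary or cerebrovascular only |
| Limited walking | Not addressed | Musculoskeletal cause only |
| Leg arteries | Not singled out | Not listed; ABI and disease history are collected |

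The list is introduced as the exclusion criteria and names specific conditions, so it reads as complete. The mismatch follows from the text alone.

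**Illustration of size**

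The article gives no share of participants with peripheral arterial disease and no AIx excess for them. The plan has no figure on this point to reproduce.

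Inputs from the article:
- Sedentary share of the cohort (Study population): w = 1,942 / 5,451 = 0.356. Sampling is proportional, so the same share applies to the sample.
- Target difference (Sample size): 3 percentage points of AIx.

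Assumed inputs:
- Overall share affected: p = 2% to 6%.
- AIx excess in those affected: d = 8 points, with 4 as an alternative.
- Frequency in the sedentary group relative to the other two groups: k = 2 or 3, or all cases sedentary.

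If the share affected is q in the other groups and kq in the sedentary group, then p = w·kq + (1 − w)·q, so q = p / (1 + w(k − 1)). The difference in shares is (k − 1)q, and the shift in the group contrast is d(k − 1)q.

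- k = 2: difference in shares = p / 1.356 = 0.737p, which is 1.5% to 4.4%. With d = 8 the shift is 0.12 to 0.35 points; divided by 3, that is 4% to 12% of the target. With d = 4 it is 2% to 6%.
- k = 3: difference in shares = 2p / 1.713 = 1.168p, which is 2.3% to 7.0%. With d = 8 the shift is 0.19 to 0.56 points, or 6% to 19% of the target.
- All cases sedentary: share in that group = p / 0.356, which is 5.6% to 16.8%. With d = 8 the shift is 0.45 to 1.35 points, or 15% to 45% of the target.

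In numbers of people, 2% to 6% of 1,500 is 30 to 90 participants.

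**The case against.** The strongest reply has four parts.

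1. **Entry is not shown.** The sample comes from an existing cohort that the Design section calls healthy, and that cohort's own entry criteria are in sources not at hand. A reader might infer that people with peripheral arterial disease are in the study. The article supports only that its rules would let them in. This part stands, and the point is worded accordingly.

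2. **An article may leave the use of ABI to a fuller document.** This also stands: the lack of a stated analysis role for ABI is not an error in itself. It does not remove the conflict between the stated population and the exclusion list, since both are set out in this article.

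3. **Arterial disease found at the visit is what the study measures.** Eligibility turns on known disease, and the intima-media section counts thickened walls and carotid plaque as abnormal findings without removing those participants. A reader might infer that everyone with a low ABI should be dropped from the main analysis. The article does not support that. It would be inconsistent with retaining people with carotid plaque and, if inactivity contributes to arterial disease, it would select on a consequence of the exposure and could pull the association towards the null. This part stands for newly found low ABI. It does not apply to disease already diagnosed before entry.

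4. **The causal harm is limited.** Methodological limitations accepts that only association can be shown. Groups A, B and C were formed on activity status from 2003 to 2006, while ethics approval for this study dates from 2009, so a low ABI at the visit need not have come before the classification. This reduces the concern for the three-group comparison. It does less for the analyses that use activity measured in the study itself by recall and accelerometer. A general caveat about causality is also no reason to leave in a source of bias that can be identified from data already being collected.

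**Conclusion.** The point holds as an inconsistency between objectives 1 and 2 and the exclusion list: known peripheral arterial disease is compatible with entry but not with the stated population. It creates a plausible route to bias in the activity-vascular association.

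The size of that bias cannot be derived from the article. About 4-12% of the 3-point AIx target is an illustration that rests on three assumptions: 2-6% affected, twice the frequency among the sedentary, and an 8-point excess. It scales directly with the assumed excess and falls to 2-6% at 4 points. A reader might take 15-45% as the expected distortion, but that requires every case to be in the sedentary group and is the extreme. Nor does it follow that the results would fail to apply to the intended population, since that depends on how many such people are present, which is unknown. The bias is probably modest; the wording conflict stands whatever its size.

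**What to change.** Reconcile the sections in one of two ways:

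- Add known peripheral arterial disease to the exclusions. If recruitment makes that impractical, exclude participants with such a recorded history from the analysis of objectives 1 and 2.
- Or narrow the population in the objectives, and the matching statements in Design and Methodological limitations, to people without known coronary or cerebrovascular disease.

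In either case, keep participants whose low ABI is discovered only at the study visit in the main analysis. Pre-specify a sensitivity analysis of the vascular outcomes without them, with the definition of low ABI fixed in advance; no cut-off is proposed here.

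The cost is one phrase in the eligibility or objectives text, one sentence on the analysis set and one additional analysis. The first option also means slightly fewer participants. No new measurement is needed, because ABI and cardiovascular history are already collected.

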#### Sample size

Sample size was estimated using AIx as a indicator of central arterial stiffness. The CAFE study[15] (ASCOT sub-study[14]) found a difference between the two groups of 6.5 (5.8-7.3) percentage points and this was associated with a difference in cardiovascular morbidity and mortality. The aim is to obtain a size sample sufficient to detect a difference of 3 percentage points of AIx between sedentary, sedentary who became active, and active subjects. There are therefore 3 study groups, assuming a standard deviation of 11, with an alpha risk of 0.05 and a beta risk of 0.20 in a two-sided test, assuming a no response rate of 20%, 352 subjects are required in each group, or a total of 1,056 subjects, but considering a proportional sample to the reference population 1,499 subjects are required. As there will be six participating groups, the sample will be 250 subjects per group for a total of 1,500 subjects, distributed in Groups A, B and C.

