#### Sample selection

The sample will be obtained from the subjects remained in the study to the assessment in 2006. Random sampling stratified by groups A, B and C will be performed to obtain a proportional size of subjects in each group for the purpose of obtaining a balanced sample.

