### Statistical analysis

Data input will be made using the Teleform system (Autonomy Cardiff Vista, California, USA), with a questionnaire previously designed for the project. Results will be expressed as mean ± standard deviation for quantitative variables or by frequency distribution for qualitative variables. The Pearson chi-square test will be used to analyze associations between qualitative variables. Student's t test for independent samples will be used to compare the means of the two groups and an ANOVA will be performed if the number of groups is increased. Post hoc comparisons will then be performed using the LSD method, with alpha < 0.05. The relationship between quantitative variables will be analyzed using Pearson's correlation coefficient. Finally, a multivariate analysis of multiple linear regression and logistic regression will be made to analyze the most significant variables (physical activity, physical fitness and dietary pattern) circadian pattern, arterial stiffness (PWV and AIx), and endothelial dysfunction (endoglin and OPG). Physical exercise will be analyzed to determine changes in cardiovascular parameters according to the dose of physical exercise performed. For hypothesis testing, an alpha risk of 0.05 will be set as the limit of statistical significance. SPSS/PC+ version 15.0 statistical package will be used (SPSS Inc., Chicago, Illinois, USA).

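### Centre is in none of the stated tests, so pooled comparisons are confounded if exposure mix and outcomes both differ by centre

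*Protocol article*

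**What the plan says.** The Design section of the protocol article describes a multicentre study run by six groups across Spain. Sample size sets the allocation across these six: "the sample will be 250 subjects per group for a total of 1,500 subjects, distributed in Groups A, B and C". Here the group that supplies 250 is a centre, while A, B and C are the activity groups.

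Sample selection names one stratification: "Random sampling stratified by groups A, B and C will be performed". Centre is not named as a stratum.

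Statistical analysis names the tests: "Student's t test for independent samples will be used to compare the means of the two groups and an ANOVA will be performed" for more than two groups, then LSD post hoc comparisons, Pearson correlation between quantitative variables, and linear and logistic regression. The regression terms named are physical activity, physical fitness and dietary pattern. Centre is mentioned in none of these.

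Quality control deals with centre operationally, through staff training and external monitoring at the six sites.

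**The concern.** A pooled comparison of A, B and C mixes differences between activity groups with differences between centres whenever the centres contribute different proportions of each group. An equal mix cannot be presumed. The cohort comes from a multicentre programme promoting physical activity (Background), and group A consists of those who became active; uptake could well have varied by site. Cohort losses were close to 20% (Methodological limitations) and a further 20% non-response is assumed (Sample size), so even a balanced draw may not give a balanced analysed sample.

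Objectives 2 and 3 are more exposed. Diet, fitness, OPG and endoglin are not sampling strata, so balance on A, B and C does not stop their levels from differing by centre. At stake are false associations in the pooled comparisons, in a study whose results are meant to inform a later trial.

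**Working it through.** **Inputs from the article.** Six centres of 250. The sizing targets are to "detect a difference of 3 percentage points of AIx between sedentary, sedentary who became active, and active subjects", "assuming a standard deviation of 11, with an alpha risk of 0.05 and a beta risk of 0.20 in a two-sided test". Non-response is 20%. The cohort mix (Study population) is A 1,163, B 1,942 and C 2,346 of 5,451, that is 21.3%, 35.6% and 43.0%.

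**The plan's own figure.** The article states: "assuming a no response rate of 20%, 352 subjects are required in each group, or a total of 1,056 subjects". Per group, n = 2 × [SD × (z₁₋α/₂ + z₀.₈) / 3]².
- At α = 0.05: 2 × [11 × (1.960 + 0.842) / 3]² ≈ 211, and 211 / 0.8 ≈ 264. This does not match.
- At α = 0.05/3, for three pairwise comparisons: 2 × [11 × (2.394 + 0.842) / 3]² ≈ 281.5, and 281.5 / 0.8 = 351.9, or 352. This matches.

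The division by three is inferred, not stated. No centre or design effect is needed to reach 352. The 1,499 for proportional sampling did not reproduce from the cohort mix, but nothing here depends on it.

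**Mechanism.** Let u_c be the deviation of centre c and f_Ac the fraction of group A that comes from centre c. The unadjusted A minus C difference then contains Σ_c (f_Ac − f_Cc) u_c. This is zero if the mix is the same in every centre or if the centres do not differ. Otherwise it is not zero in general.

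**Size for the ANOVA.** The simulation assumes no true group effect, 250 × 0.8 = 200 analysed per centre and total SD 11. It used 3,000 runs per cell (standard error √(0.05 × 0.95 / 3,000) ≈ 0.4 points). All three shares vary between centres; columns give the between-centre SD of the A share. The ICC and the spread of the mix are assumptions. Between-centre SD is 11 × √ICC: 1.1, 2.5 and 3.5 points at ICC 0.01, 0.05 and 0.10.

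Rejection rate of the 5% test without centre:

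| ICC | Same mix | SD 4 points | SD 7 points | SD 12 points |
|---|---|---|---|---|
| 0 | 4.4% | 4.7% | 5.8% | 4.7% |
| 0.01 | 4.5% | 4.9% | 6.0% | 7.3% |
| 0.02 | 4.2% | 5.5% | 6.5% | 9.8% |
| 0.05 | 4.3% | 5.9% | 8.3% | 18.4% |
| 0.10 | 3.9% | 6.7% | 12.4% | 28.2% |

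With a fixed centre term the rate is 4.4-5.8% in every cell. The 5.8% in the ICC 0 row is noise, since no inflation is possible there, so neighbouring values near 6% should not be over-read.

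A separate simulation over ICC 0.01-0.05 and an A-share SD of 0-7 points gave 4.4-6.0% unadjusted, below the 8.3% in the table. The result depends on how the mix is allowed to vary: if only the A share moves and B and C keep their ratio, inflation is smaller than when all three shares move.

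**Size for the correlations.** Take two unrelated variables with the same assumed ICC, in 6 × 200 subjects (4,000 runs each). Pooled Pearson rejects 5.2%, 6.3%, 9.7% and 21.5% of the time at ICC 0.01, 0.03, 0.05 and 0.10; adjusted for centre it stays at 4.6-5.0%. As a rough check, the variance of the pooled correlation is inflated by about 1 + 199 × ICC²: 1.02 at ICC 0.01, 1.50 at 0.05 and 2.99 at 0.10. Equal centre sizes do not prevent this.

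**The case against.** The strongest reply is that the harm is conditional and the article shows neither condition. It reports no activity mix by centre and no between-centre variation. With an equal mix the unadjusted ANOVA is unbiased and slightly conservative. The Sample size sentence can also be read as splitting each centre's 250 across A, B and C, which would make the mix about equal. These points stand, and they rule out any single figure for the error rate. They do not cover correlations with diet, fitness or biomarkers, which are not sampling strata.

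A reader might infer that the fixed blocks of 250 cause the distortion, or that the error rate is shown to be wrong. The article supports neither. Equal centre sizes are harmless in themselves, and inflation needs mix and outcome both to differ by centre. The strong cases in the table are strong: at ICC 0.10 the between-centre SD of 3.5 points exceeds the 3-point difference the study is sized to detect.

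Measurement controls also count. AIx uses one device and software type at all sites, carotid thickness is read automatically by two trained investigators, and OPG and endoglin are assayed in one laboratory. These reduce measurement differences between centres but do not remove differences between their populations.

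Lastly, a condensed article may leave adjustment covariates to a fuller plan. That is fair for the regressions, and the word ANOVA does not exclude a centre factor. It is less persuasive for the t test and the Pearson correlation, which are named and cannot carry a centre term.

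**Conclusion.** The point holds as a conditional weakness with a cheap remedy. The article does not say that A, B and C are drawn within centre, and it writes its group comparisons and correlations without centre. If exposure mix and outcome both vary by centre, the pooled results are confounded. For the three-group ANOVA the type I error ranges from no inflation (equal mix or zero ICC), through about 5-6% under mild assumptions, to above 10% under strong ones. Every figure beyond the no-inflation case rests on an assumed ICC and mix variation. For the regressions the point is weaker, because a fuller covariate list may exist elsewhere.

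**What to change.** 1. In Sample selection, state that A, B and C are drawn proportionally within each centre.
2. In Statistical analysis, for outcomes measured at all six centres, replace the t test and one-way ANOVA by a model with activity group and centre as fixed factors, and base the post hoc comparisons on centre-adjusted means.
3. Include centre in the linear and logistic regressions of those outcomes, and replace pooled Pearson correlations by partial correlations adjusted for centre.
4. Exempt the SphygmoCor PWV and central AIx. The Pulse wave analysis section places these only in the Salamanca cohort, so a six-level factor cannot be estimated for them.

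Step 2 is still needed if step 1 is adopted, because non-response can unbalance the analysed sample. The cost is five degrees of freedom out of about 1,200 analysed subjects (1,500 × 0.8) and a sentence or two of text. No extra subjects or measurements are needed.
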